	**Study period**				
	**Enrolment**	**Allocation**	**Post-allocation**		
**Timepoint**	*** − t***_**0**_	** − *****t***_**0**_	**t**_**0 *1**_	***t***_**1 *2**_	***t***_**2 *3**_
**Enrolment:**					
** Eligibility screen**	X				
** Informed consent**	X				
** Allocation (cluster randomisation)**		X			
**Interventions:**					
*** On-site health counselling***				X	
*** Online health counselling***				X	
*** Waiting control group (does not receive counselling intervention)***					
**Assessments:**					
*** Health behaviour***			X		X
*** Health knowledge***			X	X	X
*** Customer satisfaction and usability***				X	X

^*^1 — should be answered up to 24 h before the counselling (control group – soon after receiving the questionnaire)

^*^2 — directly after the consultation (only for the intervention groups)

^*^3 — 6 weeks after *t*0

#### The three study arms

The three study arms are outlined in this section. Participants receiving the on-site intervention (arm one) will receive counselling for 45 min at a local health centre. The counsellors will use an information brochure on the impact of LRRFs during pregnancy and a conversation guide to support the process. Following this, the participants will be given the information brochure to take home.

In the online intervention (arm two), participants will engage with a 45-min online counselling session via a screensharing system with a video facility. The counsellors will share a digital PDF containing important information about the impact of LRRFs during pregnancy. The counselling process will also be supported by short videos of expert interviews (approx. 1 min per video), where relevant experts will provide information on the topics of nutrition, physical activity, relaxation, stress management, and substance use. Counsellors will receive a conversation guide to structure the counselling, and the participants will receive their information brochures via postal mail following the session.

Participants in the waiting-list control (arm three) will not receive counselling during the intervention period. However, at 6 weeks post-intervention, and after completing the *t*2-questionnaire, they will be invited to participate in online or on-site counselling and/or to receive the information brochure via mail.

All participants will have the option to terminate their participation in the study via a digital form on the AOK Baden-Wuerttemberg website. Table 2 summarises the three interventions.

**Table 2 Tab2:** A summary of the three interventions of the study and the corresponding resource materials employed

On-Site Intervention, study arm 1	Online Intervention, study arm 2	Waiting-list Control, study arm 3
45-min on-site counselling at health centres covering the impact of LRRFs during pregnancy Materials • Information brochure provided for participants • Conversation guidelines provided for the counsellors	45-min online counselling covering the impact of LRRFs during pregnancy Materials • Interactive PDF shown via screen-sharing • Expert and explanatory videos • Information brochure mailed to participants • Conversation guidelines provided for the counsellors	No consultation about LRRFs Optional online or on-site consultation following full data collection (*t*2); the information brochure can be requested separately

#### Content of the counselling resources

Content of used resources for supporting participants and counsellors is based on the current scientific recommendations for nutrition, physical activity, relaxation, stress management, and substance use during pregnancy. This content was compiled from the guidelines published by relevant institutions and professional societies [15–17] and the current research evidence regarding LRRFs during pregnancy. These study resources were subsequently discussed and summarised by researchers at the Heidelberg University Hospital, Germany, and then prepared for inclusion in the counselling sessions. Several experts further reviewed and modified the content as necessary. This process is intended to ensure content consistency in all subject areas pertaining to the study and provides a valid platform for comparison of the three study groups. The design and finalisation of the resource materials were performed in collaboration with service providers associated with AOK Baden-Wuerttemberg.

#### Training for counsellors

Study counsellors must independently complete a 4-h e-learning module detailing the context and application of information on the study design and procedure, and the relevant scientific information on the relationship between LRRFs and pregnancy. The successful completion of the e-learning module requires an 80% minimum test score in a following multiple-choice assessment. Approximately 50 counsellors are expected to participate in the training. The e-learning module was developed by an external service provider associated with AOK Baden-Wuerttemberg.

Where medical questions and topics surpass the expertise and competencies of the counsellors, participants will be referred to the relevant care-pathway.

### Monitoring of the intervention process

Researchers from Heidelberg University Hospital will be available for consultation with the counsellors throughout the intervention period. In order to ascertain if the planned process will work as part of the counsellor’s daily routine, feedback will be sought from the counsellors after the initial health education sessions. If problems arise, the process, or the procedures, will be adjusted accordingly.

### Study outcomes

#### Primary outcomes

The study has two co-primary outcomes. The two primary outcomes of this study are health knowledge, and health-related behaviours, relating to LRRFs (nutrition, physical activity, relaxation and stress management, and substance use) during pregnancy.

Health Knowledge: Participants’ health knowledge related to LRRFs during pregnancy will be measured by a questionnaire developed by Oechsle et al. [8]. This questionnaire was developed to assess knowledge and attitudes of pregnant women concerning alcohol consumption, smoking, nutrition, physical activity, oral health, and medication. The questionnaire has been modified for the AOK-Family + study. In this process, an additional option (uncertain) was added to the previously dichotomous answer options (yes/no), and the individual wording of questions was adjusted. In addition, questions about oral health were replaced with questions about relaxation behaviours.

Health-Related Behaviours: Health-related behaviours have multifaceted domains. In this study, it will be assessed concerning nutrition, physical activity, relaxation and stress management, and substance use. As no all-encompassing instruments exist for this specific purpose, existing instruments for measuring health-related behaviours with regard to nutrition, physical activity, relaxation, stress management, and substance use were tested; those deemed suitable were adopted with a few adjustments according to the needs of the study. The final survey instrument is based on the AUDIT-C questionnaire, which is used to measure alcohol consumption [18, 19], and parts of the questionnaire from the study “German Health Update” (GEDA 2014/2015) by the Robert Koch Institute [20]. These parts relate to the assessment of physical activity (European Health Interview survey—Physical Activity Questionnaire (EHIS-PAQ)) [21] and tobacco use [20]. The Stress and Coping Inventory (SCI) [22] will be used to measure active stress management. Measurements on dietary behaviour were developed for this study. Changes in health behaviours are considered at the level of each category (physical activity, relaxation and stress management, and substance use).

##### Pilot testing and validation of the questionnaires

The questionnaires were piloted and validated in three consecutive steps. An expert interview was conducted with two midwives to verify the content and ensure the face validity of the questionnaire. Each topic in the questionnaire was discussed. The revised questionnaire was then iteratively piloted with seven women. The focus was on feasibility, comprehensibility and usability of the questionnaire. Finally, an empirical investigation was carried out in form of a cross-sectional study with 79 pregnant women. The plausibility of the results was assessed by reviewing the existing literature.

#### Secondary outcomes

##### Client satisfaction and user-friendliness

The secondary outcomes include client satisfaction, practicability and user-friendliness of the consultations. These will be evaluated using existing internal (not published) standard questions from AOK Baden-Wuerttemberg regarding customer satisfaction. The topics included are satisfaction with the enrolment process, satisfaction with the counsellor’s engagement, satisfaction with the counselling itself, possible recommendations for the counselling, and the subjectively perceived benefit of the counselling. This information is recorded using a 5-point Likert scale (strongly agree–strongly disagree). Mean values of the individual statements are then calculated and compared with previous internal results. These questions will only be addressed to the intervention groups (study arm one and two).

#### Other measures

All participants will be asked questions to determine their socio-demographic status. These include age, education, occupation, country of birth, parents’ countries of birth, and household income.

### Participant timeline, data collection, and management

Following verbal informed consent, a consultation appointment will be arranged for the intervention groups, and the participants will receive access (QR-Code and URL) to the first online questionnaire (*t*0), which will also be posted by mail. Verbal informed consent is recorded by the project team of AOK Baden-Wuerttemberg. Before starting the questionnaire, the participants’ consent is obtained again by actively ticking a checkbox. This baseline questionnaire should be answered up to 24 h before the counselling session (duration approximately 20–30 min) and will capture their socio-demographic data, health knowledge, and health-related behaviours. At the appointment, before the start of the counselling session, the participants will be asked whether the baseline questionnaire (*t*0) has already been completed. If not, completion of the questionnaire will be requested prior to counselling. Otherwise, the counselling intervention (on-site/digital) will take place and will last for approximately 45 min. Immediately after counselling, the counsellors will provide participants with access (QR-Code and URL) to the second online questionnaire (*t*1) to measure the short-term effect of the counselling on health knowledge, together with information regarding client satisfaction and the user-friendliness of the counselling (secondary outcomes) (duration 10 min). This questionnaire should be completed directly after counselling at the health centres or after leaving the digital room.

To measure the longer-term effects of the counselling, a follow-up questionnaire 6 weeks after *t*0 will be conducted, including participants’ health knowledge and healthy behaviours (*t*2), as well as their perceived user-friendliness and client satisfaction (duration approximately 30–35 min). The participants will receive access (QR-Code and URL) to the last online questionnaire by mail.

The waiting-list control group will receive access (QR-Code and URL) to the baseline questionnaire after they gave consent for study participation and receive the last questionnaire (*t*2) 6 weeks later by mail. After completion of the follow-up survey, the participants in the control group can individually arrange a requested AOK-Family + consultation. Table 3 summarises the timing and content of the questionnaires for each study arm.

**Table 3 Tab3:** Summary of the timing and content of the questionnaires for each study arm (primary outcomes are highlighted)

	**On-site intervention, study arm 1**	**Online intervention, study arm 2**	**Waiting-list control, study arm 3**
***T*****0 (posted by mail; answered up to 24 h before the counselling)**	Socio-demographic data, **health knowledge, health-related behaviours**	Socio-demographic data, **health knowledge, health-related behaviours**	Socio-demographic data, **health knowledge, health-related behaviours**
***T*****1 (directly after counselling, access via QR-Code/URL)**	**Health knowledge**, client satisfaction user-friendliness of the counselling	**Health knowledge**, client satisfaction user-friendliness of the counselling	
***T*****2 (posted by mail, 6 weeks after *****t*****0)**	**Health knowledge, healthy behaviours** user-friendliness, client satisfaction	**Health knowledge, healthy behaviours** user-friendliness, client satisfaction	**Health knowledge, healthy behaviours** user-friendliness, client satisfaction

All data will be collected anonymously using the online survey system LimeSurvey. The digital questionnaires can be filled out on personal smartphones or personal computers. Personal data, for identification as an AOK Baden-Wuerttemberg insured client, will be managed by AOK Baden-Wuerttemberg in accordance with their data protection standards. The Department of General Practice and Health Service Research (University Hospital Heidelberg) will only receive anonymous data from the questionnaires. The storage of this data occurs on a computer that is at least externally twofold encrypted and is protected against unauthorised access. Only researchers at Heidelberg University Hospital involved in the study have access to this data. A code created by the participants themselves at the beginning of each questionnaire enables the questionnaires from the different survey periods to be assigned accordingly. This code has five digits and is determined by four questions on invariable characteristics of the participants. Anonymity is preserved as the code remains exclusively with Heidelberg University Hospital and thus does not allow the person to be identified.

In order to generate robust data sets, the intervention will only start after the baseline questionnaire (*t*0) has been completed, and the second questionnaire will be directly administered during the appointment (*t*1). An independent person will be involved to monitor and check the integrity of data. To reduce the drop-out rate for the 6-week follow-up, participants will receive a reminder after 7 weeks and the incentive only after full participation. Participation is considered successful as soon as questionnaire *t*3 has been completed. This allows recording a change in health behaviour and health knowledge over a period of 6–7 weeks. Figure 2 illustrates the study design and process.

**Fig. 2 Fig2:**
[figure not shown]
The study design with data collection and participant timelines

### Sample size calculation

The power calculation was performed assuming a probability of successful participation by 50% of participants in the control group, and a perceived relevant improvement of the successful participation by 65% of participants in the intervention groups. These assumptions were based on the results of a cross-sectional study by Oechsle et al. [8] on the health knowledge of pregnant women regarding LRRFs, in which knowledge gaps and their health effects were identified, and on studies indicating the need for improvement in the health behaviours of pregnant women [5–7, 23]. We calculated the sample size for the primary outcome “health knowledge” because for this outcome, we could derive a valid effect size from previous studies.

Furthermore, sample size calculations were based on a power of (1 − *ß*) = 65% and a significance level of *α* = 5% (two-sided).

To account for the cluster structure, with participants nested within customer and service centres, a small intra-cluster correlation coefficient (ICC) of 0.01 was assumed. As there are 14 district directorates of AOK Baden-Wuerttemberg (arm one = 4, arm two = 5, arm three = 5), it is estimated that there would be approximately 36 participants per cluster (cluster = district directorate). Based on these assumptions and the perceived relevant difference of 50% in the control versus 65% in the intervention group, the sample size per study arm will be *n* = 168. This implies a total sample size of *n* = 504. A dropout rate of 20% is assumed; therefore, *n* = 638 participants must be enrolled in the study at time *t*0 to reach *n* = 504 for analysis.

The above calculations were performed using R (Version 1.3.5) and the sjstats package (Version 0.18.1).

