### Randomisation process

The 14 district directorates of AOK Baden-Wuerttemberg (Fig. 1), in Southwest Germany, are randomly assigned to one of the three study groups: the on-site intervention group, the online intervention group, or the control group. The initial randomisation process has been performed via computer generation and was carried out using a simple cluster-randomised design before the process of enrolment. The cluster randomisation will be conducted by an independent operator using the statistical program R (Version 1.3.5) with the randomizr package. The conduct of randomisation was concealed to the members of the study team. Similarly, the counsellors will be allocated according to their place of employment. Depending on where the insured people live, they will be assigned to the appropriate district directorate (e.g. if an insured person lives in the Ludwigsburg-Boeblingen area, she will be assigned to the Ludwigsburg-Boeblingen district directorate and the staff employed there). If an insured person is interested in the study, she will receive the intervention assigned to the responsible district directorate (e.g. insured person lives in the Ludwigsburg-Boeblingen area. The area has been assigned to intervention arm 1. The insured person is therefore automatically assigned to intervention arm 1). This means that the district directorates should be considered as randomised units.

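### The 65% power allows for clustering only through a design effect; on its own unadjusted inputs, a reference based on 9 or 10 directorates per comparison gives about 55-60%

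*Protocol article*

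**What the plan says.** The Randomisation process section leaves no doubt about the unit: "This means that the district directorates should be considered as randomised units". The Statistical analysis section compares each of the two intervention arms with control. The primary model has random coefficients for directorates and adjusts for the baseline value.

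The Sample size calculation section is built on health knowledge. Its inputs are:
- control success: "assuming a probability of successful participation by 50% of participants in the control group";
- intervention success: "perceived relevant improvement of the successful participation by 65% of participants in the intervention groups";
- power, in per cent: "sample size calculations were based on a power of (1 − *ß*) = 65";
- test: "a significance level of *α* = 5% (two-sided";
- clustering: "a small intra-cluster correlation coefficient (ICC) of 0.01 was assumed", and "it is estimated that there would be approximately 36 participants per cluster (cluster = district directorate";
- allocation of directorates: "As there are 14 district directorates of AOK Baden-Wuerttemberg (arm one = 4, arm two = 5, arm three = 5".

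The result is 168 per arm and 504 in total. The section prints no formula. It uses the count of directorates only to arrive at a cluster size, and mentions no adjustment for how few there are.

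**The concern.** A design effect corrects the variance of the arm difference for clustering. It does not correct for having to estimate the between-directorate variance from a handful of directorates. With 4 v 5 or 5 v 5 randomised units, the two-sided 5% critical value is 2.36 on 7 degrees of freedom, 2.31 on 8, or 2.20 on 11 if all three arms share one variance. The large-sample value is 1.96. A power figure that ignores this is too favourable.

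The section also gives one figure for both comparisons, although the on-site comparison has fewer directorates. Its two size statements do not fit together either: four directorates of 36 make 144 and five make 180, not 168. The starting power is already low, so a further overstatement affects how a non-significant result should be read, most of all for on-site v control.

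**Working it through.** **Inputs**, all from the Sample size calculation section: p0 = 0.50, p1 = 0.65, difference 0.15, two-sided 5%, ICC 0.01, about 36 per directorate, directorates 4/5/5, 168 per arm.

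**Reproducing the plan's figure.** The standard two-proportion formula at 65% power gives 120 per arm before clustering.
- Design effect with 36 per cluster: 1 + 35 × 0.01 = 1.35, and 120 × 1.35 = 162. Conversely, 168/1.35 = 124.4 gives a power of 67.0%.
- Design effect with 42 per cluster (168/4): 1 + 41 × 0.01 = 1.41, and 120 × 1.41 = 169.2. Conversely, 168/1.41 = 119.1 gives a power of 65.0%.
- A two-sample t-test with a standardised difference of 0.30 (assumed) needs 123.2 per arm. Inflated for 9 clusters at ICC 0.01 it totals 335.9, or 168 per arm.

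The last two match best. Which route was taken cannot be told from the document, but all of them inflate for clustering and none has a term for few clusters.

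**Adding the cluster degrees of freedom.** With design effect DE:

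SE = √[DE × (0.65 × 0.35/n1 + 0.50 × 0.50/n0)], and noncentrality = 0.15/SE.

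Power comes from the noncentral t. The degrees of freedom are the clusters in the comparison minus 2 (7 on-site, 8 online), or 14 − 3 = 11 for a three-arm model with common variance. At 168/168 and DE 1.35: SE = √[1.35 × (0.2275 + 0.25)/168] = 0.0619 and noncentrality 2.42.

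| Comparison | n | Normal | 7 or 8 df | 11 df |
|---|---|---|---|---|
| On-site v control | 168/168 | 68% | 55% (7) | 60% |
| Online v control | 168/168 | 68% | 57% (8) | 60% |
| On-site v control | 144/180 | 66% | 53% (7) | 58% |
| Online v control | 180/180 | 71% | 60% (8) | 63% |

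Design effects specific to each arm at 168 per arm (1.41 for four clusters of 42, 1.326 for five of 33.6) give 54.5-59.3% on-site and 57.4-60.5% online, so the picture is the same.

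**Simulation.** Beta-binomial data analysed by a cluster-level t-test (40,000 runs) gave a power of 53.1-53.3% on-site and 57.1-59.5% online. Type I error was 5.0-5.2%, so the t reference is well calibrated here.

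**Sensitivity** (assumed values; 144/180 and 180/180; range from 7 or 8 to 11 df).

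| Change | On-site | Online |
|---|---|---|
| ICC 0.005 | 59-64% | 65-69% |
| ICC 0.02 | 44-49% | 50-53% |
| ICC 0.05 | 30-33% | 34-36% |
| ICC 0.01, cluster-size CV 0.6 | 50-54% | 56-59% |
| ICC 0.01, t0-t2 correlation 0.3 | 57-62% | 64-67% |
| ICC 0.01, t0-t2 correlation 0.4 | 60-65% | 67-70% |
| ICC 0.01, t0-t2 correlation 0.5 | 65-70% | 72-75% |

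The correlation rows multiply the variance by (1 − r²), which is a simplification for a clustered binary outcome.

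**The two size statements.** Both 3 × 168 and 14 × 36 equal 504, so the total agrees. The arms do not: 4 × 36 = 144 and 5 × 36 = 180. For 168 in each arm, the on-site directorates must average 42 and the others 33.6.

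**The case against.** The strongest reply is that the planned analysis is not the unadjusted contrast computed above. The Primary outcomes part of the Statistical analysis section adjusts for the t0 value, and the same questionnaire is repeated after six weeks, so a correlation of zero is the pessimistic extreme. At an assumed correlation of 0.5, every comparison reaches 65% or more. This stands. A reader might infer that the trial delivers only 53-63% power, but the document gives no correlation and does not support that. Equally, the stated calculation uses no baseline correlation, so the adjustment cannot be what supports its 65%.

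A reader might also infer that the on-site arm is planned at 144. The document says 168 per arm and calls 36 approximate. The Process evaluation section gives 426 in the two intervention groups, close to two thirds of 638 (425.3) and not to nine fourteenths (410), which points to equal arms. The 53% is therefore conditional on 36 per directorate.

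The same section describes knowledge as a summed score as well as in dichotomous terms. If the score is analysed, neither the stated 65% nor these figures describe that test. The small-sample method of the mixed model may properly be left to the analysis plan, which is why a range of 7 to 11 degrees of freedom is shown. Finally, the protocol openly states a low power and calls the study exploratory in part. That lowers the weight of the point, but the Objectives section also says that testing is aimed at superiority.

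**Conclusion.** The point holds as a statement about the stated calculation. On its own inputs, with equal clusters and no baseline adjustment, allowing for the number of directorates brings 65% down to about 55-60% at 168 per arm. If directorates average 36, it is about 53-58% for on-site v control and 60-63% for online v control. No pairwise variant at ICC 0.01 reaches 65% without baseline adjustment.

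That the calculation used a design effect alone is inferred from what reproduces 168, since no formula is printed. The true power of the adjusted analysis is unknown from this document and may be lower or higher than 65%. The severity is moderate: one stated figure is too favourable on its own terms, and the arm and cluster sizes need reconciling, but neither the design nor the analysis is invalidated.

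**What to change.** In the Sample size calculation section:
- Restate power separately for on-site v control and online v control, using cluster degrees of freedom, and label the figures as unadjusted for baseline.
- Add a short table over ICC (for example 0.005-0.05), cluster-size variation (for example CV 0-0.6) and an assumed t0-t2 correlation (for example 0-0.5).
- Say whether 168 per arm or about 36 per directorate is the planning assumption, and give the implied sizes for arms with 4 and 5 directorates.
- State that results will be interpreted through confidence intervals.

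Enlargement is not proposed: the 14 directorates are fixed, and recruitment was due to end on 30 June 2024. The cost is one paragraph and a small table, with an unadjusted power less favourable than the present figure. Nothing in the conduct of the trial changes.

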### Study population

Initially, all participants in the intervention groups (*n* = 426) will be asked additional questions about the materials provided in the consultation.

Furthermore, interviews (*n* = 20–25) and two focus groups (*n* = 7 each) with trained study counsellors from AOK Baden-Wuerttemberg will be conducted to assess procedures and processes. All counsellors will be recruited via a shared e-mail distribution list created specifically for the purposes of the project.

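### The enrolment target of 638 does not follow from 504 with 20% dropout (that gives 630), and equal arms of 168 are not what a 4/5/5 split of directorates would be expected to yield; minor, with little effect on power

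*Protocol article*

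**What the plan says.** All but one of the figures stand in the Sample size calculation section of the protocol article. It plans for a "perceived relevant difference of 50% in the control versus 65% in the intervention group", with 65% power and two-sided α of 5%, and for clustering "a small intra-cluster correlation coefficient (ICC) of 0.01 was assumed". It lists 14 district directorates, four in the on-site arm and five each in the online and control arms, and expects roughly 36 women in each. From these assumptions it concludes that "the sample size per study arm will be *n* = 168", which makes 504 in total. The last step is the allowance for dropout: "A dropout rate of 20% is assumed; therefore, *n* = 638 participants must be enrolled in the study" at baseline so that 504 can be analysed.

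One further figure depends on these. Under Process evaluation, Study population, the additional questions on materials go to "all participants in the intervention groups (*n* = 426").

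**The concern.** Two things do not fit. The enrolment target is presented as a consequence of 504 and 20%, yet those two numbers give another result. And the section sets an unequal allocation of directorates beside equal arm sizes without saying how four directorates are to supply as many women as five. The totals agree, because 3 × 168 and 14 × 36 are both 504, so the mismatch between arms is easy to miss.

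At stake are the recruitment target, the planned arm sizes against which achieved numbers will be reported, and the denominator announced for the process evaluation. Women enter the arm of the directorate where they live (Randomisation process), so arm sizes depend on recruitment in each directorate and are not fixed centrally.

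**Working it through.** **Inputs, all from the Sample size calculation section unless noted.** Proportions 0.50 and 0.65; power 65%; α 5% two-sided; ICC 0.01; directorates 4/5/5; about 36 women per directorate; 168 per arm; 504 in total; dropout 20%; 638 to enrol. From Process evaluation, Study population: 426 in the intervention groups. I read 36 as women analysed, because 14 × 36 = 504.

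**1. The 168 per arm.**
- Design effect: 1 + (36 − 1) × 0.01 = 1.35.
- Pooled two-proportion formula: 120 per arm, and 120 × 1.35 = 162.
- With a standardised difference of 0.3 (0.15 over an SD of 0.5, my assumption), a t-test needs 246.4 women in two arms before clustering. With 4 + 5 = 9 directorates in the comparison, the cluster size is 246.4 × 0.99/(9 − 246.4 × 0.01) = 37.3. The total is 246.4 × (1 + 36.3 × 0.01) = 335.9, or 168 per arm.

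So 168 can be reproduced as a power requirement.

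**2. The dropout step.**
- Required enrolment = analysed/(1 − dropout) = 504/0.80 = 630. The result is the same by arm (3 × 168/0.80 = 3 × 210) and by directorate (14 × 36/0.80 = 14 × 45).
- The common mistaken form, 504 × 1.2, gives 605, so it does not explain 638 either.
- 504/0.79 = 637.97, and 1 − 504/638 = 0.210. The printed target matches a dropout of 21%.
- Difference: 638 − 630 = 8, and 8/630 = 1.3%. Enrolling 638 and losing 20% leaves 638 × 0.80 = 510, which is above 504.

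**3. Arm sizes under 4/5/5.**

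| | On-site | Online | Control | Total | Intervention arms |
|---|---|---|---|---|---|
| Directorates | 4 | 5 | 5 | 14 | 9 |
| Analysed at 36 each | 144 | 180 | 180 | 504 | 324 |
| Enrolled (÷ 0.80) | 180 | 225 | 225 | 630 | 405 |

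Equal arms of 168 would need 168/4 = 42 per on-site directorate and 168/5 = 33.6 in each of the others.

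**4. The 426.**
- Equal thirds: 638 × 2/3 = 425.3. By arm, 168/0.79 = 212.7, rounded up to 213, and 2 × 213 = 426.
- Under 4/5/5 with equal recruitment: 630 × 9/14 = 405, or 638 × 9/14 = 410.

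**5. Power, pooled formula.** Effective n = n/1.35. Power = Φ[(0.15 − 1.96 × SE₀)/SE₁], with SE₀ from the pooled proportion and SE₁ from the two separate ones.

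| Comparison | n | Effective n | SE₀ | SE₁ | Power |
|---|---|---|---|---|---|
| Equal arms as stated | 168 v 168 | 124.4 v 124.4 | 0.0627 | 0.0619 | 67.0% |
| Control v on-site | 180 v 144 | 133.3 v 106.7 | 0.0644 | 0.0633 | 64.7% |
| Control v online | 180 v 180 | 133.3 v 133.3 | 0.0605 | 0.0598 | 70.0% |

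**The case against.** The strongest reply is that nothing here harms the trial. The target of 638 is too high rather than too low, so a team that meets it still analyses 504 or more at 20% dropout. The figure of 168 is offered as the result of a power calculation, not as a product of directorates and 36, and it can be reproduced as such. The figure of 36 is called approximate and equals 504/14, so it is a planning mean and not a quota. Nothing in the article says that directorates are equal in size, so 144/180/180 is a projection. The 426 is simply two thirds of 638, rounded up, and no test of a primary outcome rests on it.

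Most of this stands, and it sets the size of the point. It does not remove it. The 20% and the 638 are joined by a therefore that is false. Equal arms under 4/5/5 need on-site directorates to recruit 25% more than the others (42 against 33.6), and the article gives no reason to expect that. That 426 follows from equal thirds shows only that the unequal allocation was left out a second time.

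A reader might go further and infer that the on-site arm is 24 women short and the on-site comparison therefore underpowered, or that the sample size section as a whole fails to reconcile. The article does not support either inference. The shortfall arises only if directorates recruit equally, the power is then still within half a percentage point of the stated 65%, and the totals agree.

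**Conclusion.** The point holds and is minor. The enrolment target is wrong as derived: 630 follows from the stated 20%, and 638 needs 21%. The error is 8 women, in the conservative direction. The equal arms of 168, and the 426 built on equal thirds, are not what the stated allocation yields on average. With equal recruitment across directorates the expected numbers are 144/180/180 analysed and 180/225/225 enrolled, and the intervention arms hold about 405 enrolled women, 21 fewer than printed (16 fewer if 638 is kept and split 9/14).

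On-site against control loses practically nothing against the stated power, and online against control gains. What the equal-arm figure hides is that the two comparisons with control are not equally powered.

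These results assume directorates of equal yield, the stated ICC of 0.01, a design effect of 1.35 throughout, and the pooled two-proportion formula. The actual yield per directorate is not given and could move the arm sizes either way.

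**What to change.** - In Sample size calculation, restate the enrolment target as 630, or keep 638 and state the 21% dropout that it implies.
- Keep 168 per arm as the requirement from the power calculation. Replacing it by a recruitment projection would confuse what is needed with what is expected.
- Beside it, give the expected numbers per arm under 4/5/5 (144/180/180 analysed if directorates recruit equally) and the power of each comparison with control (about 64.7% on-site, about 70% online).
- In Process evaluation, Study population, make 426 consistent with the chosen total and the allocation: about 405 under equal recruitment with a total of 630.

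This costs a few sentences of text. No new directorate quotas are needed. They would be an operational change for almost no power, and the Trial status section has recruitment closing on 30 June 2024, under three weeks after the date of this protocol version (11 June 2024). The text should be settled before achieved arm sizes are reported against the plan.
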